**Methods:**

In this study, healthy controls, prodromal diabetes and diabetes subjects (53 subjects/group) aged 40-60 years will be recruited from the physical examination center of Tangdu Hospital. The neuroimaging and psychometric measurements will be repeated at a 0.5 year-interval for 2.5 years’ follow-up. The primary outcome measures are 1) Microstructural and functional alterations revealed with multimodal MRI scans including structure magnetic resonance imaging (sMRI), resting state functional magnetic resonance imaging (rs-fMRI), diffusion kurtosis imaging (DKI), and three-dimensional pseudo-continuous arterial spin labeling (3D-pCASL); 2) Cognition evaluation with MoCA. The second outcome measures are obesity, metabolic characteristics, lifestyle and quality of life.

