### Sample size calculation and statistics

Power calculations have been estimated with reference to other studies that used similar end points [21, 29], according to the formula for estimating the variances of mean values from multiple groups [29]. A sample size of 40 patients per group will be suitable with a power of 0.8, an alpha significance level of 0.05 (two-side). In our group, longitudinal changes of this effect size have been shown previously in groups larger than 10 subjects. Given a drop-out ratio of included subjects, at 25 %, into account, the total sample size is 53 in each group.

Demographic clinical, laboratory, cognitive, and neuropsychological data will be analyzed using SPSS 22.0 (SPSS, Inc.). One-way analysis of variance or *χ*^2^ test will be used to explore differences of these data among three groups (HC, prodromal diabetes and diabetes). Neuropsychological difference among them will be performed with analysis of covariance (ANCOVA) using demographic factors (gender, age, and years of education) as covariates. *Post-hoc* comparisons will then be performed with all demographic factors (gender, age, and years of education) as covariates. *P* < 0.05 is considered as significant. It is reported ReHo and ALFF values are affected by the structure alterations (e.g., atrophy) [30]. We will take ventricular volume as a covariance to rule out such influence.

For images analysis, one-sample t tests will be performed on the individual corresponding maps for each group using SPM12 to explore the differences within groups. Dunnett-*t* test will be performed for differences among case groups and healthy control group. The statistical threshold of the two test will both be set at *P* <0.005 which corresponded to a corrected *P* <0.005 (multiple comparisons with family-wise error).

Linear regression analysis is performed across the T2DM groups and prediabetes groups to assess relationships between imaging values and cognitive testing scores. When the most sensitive parameters are found, a receiver operating characteristic (ROC) curve will be generated to achieve the sensitivity and specificity of the certain parameter for early detection of the cognitive decline.

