## Discussion

The current study evaluates various characteristics of diabetes, especially the central nervous system image presentations in different stage of diabetes progression, and aims to establish an imaging evaluation system for detecting and evaluate MCI in diabetes. Benefits and limitations of this study are discussed below.

It is reported by most researchers that diabetes result in regional hypoperfusion. However, Henry Rusinek and his colleagues found that no hypoperfusion exists in diabetes group, in contrast to hypoperfusion in insulin resistant but not diabetes group [29]. Since insulin resistant is one of main mechanisms of diabetes, we are still uncertain why the perfusion data differs between the two groups. The current study will follow up individual’s characteristics in various areas, especially the image presentation for not less than 3 years. Natural progression of diabetes is monitored. Reperfusion or compensation result in diabetes will be explored. We may discovery the unrevealed mechanism for the divergent between IR and diabetes group.

Structure changes are common in advanced T2DM. It may also exist at prediabetes stage. The volume changes should be used to be one of the covariant to prevent its effect to signal intensity. In current study, we take cerebral ventricle volume, which may represent the structure changes of the whole brain, as a covariant. DKI reveals the non-Gaussian characteristics of gray and white matter [31]. Imaging reports of this respect in diabetes are limited. We undergo the examination of DKI, instead of DTI to explore the real world of microstructure.

Various imaging researches of diabetes have been reported. Most of them are studies of one or two protocols. In our study, multi-modal sequences will be conducted and analyzed at the same time. It may be revealed which one or combined protocols may express the highest area under curve by drawing ROC curve. Corresponding sensitivity and specificity are calculated, and then we will get the cutoff values to diagnose MCI.

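### The regression relating imaging values to cognitive scores names no covariate, although the same scores are adjusted for gender, age and education in the ANCOVA, so its slopes can mix demographic gradients with a cognition-related signal

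*Protocol article*

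**What the plan says.** All the analyses concerned are in the protocol article, under Sample size calculation and statistics.

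- Group comparison of the cognitive scores: "Neuropsychological difference among them will be performed with analysis of covariance (ANCOVA) using demographic factors (gender, age, and years of education) as covariates".
- Post-hoc tests carry the same set: "comparisons will then be performed with all demographic factors (gender, age, and years of education) as covariates".
- A further covariate is introduced because structural change affects ReHo and ALFF: "We will take ventricular volume as a covariance to rule out such influence".
- Imaging against cognition, in the two case groups: "Linear regression analysis is performed across the T2DM groups and prediabetes groups to assess relationships between imaging values and cognitive testing scores". No covariate is named.
- The next sentence moves to diagnostic accuracy: "When the most sensitive parameters are found, a receiver operating characteristic (ROC) curve will be generated to achieve the sensitivity and specificity".

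The Discussion gives the purpose of the ROC: "Corresponding sensitivity and specificity are calculated, and then we will get the cutoff values to diagnose MCI". It also says that the ROC curves may show which MRI protocol, or which combination, has the largest area under the curve.

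The abstract sets the population: "diabetes subjects (53 subjects/group) aged 40-60 years will be recruited". The inclusion criteria set a senior-high-school minimum for education and no upper limit. No matching on age or education is described.

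**The concern.** By adjusting the cognitive scores twice for gender, age and education, the plan treats these factors as determinants of the scores. In the statistics section, the regression is the analysis that relates imaging values to those scores, and there the three factors are not mentioned. Several of the listed imaging measures (atrophy, white matter lesions, diffusion indices, cerebral blood flow) can plausibly vary with age over a 20-year span. If such a measure and the cognitive score both move with age or schooling, an unadjusted slope differs from zero even when the measure says nothing about cognition beyond the demographics.

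Restricting the model to the two case groups does not prevent this, and neither would a group term, because the gradient also exists within a group. If the regression decides which parameters go forward, a marker of age or schooling could reach the ROC, and part of its apparent accuracy would then be accuracy in predicting the demographic factor.

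**Working it through.** **Inputs from the protocol article.** 40 evaluable subjects per group, a 25% drop-out allowance and 53 enrolled per group. The regression uses two groups, so n = 2 × 40 = 80 evaluable or 2 × 53 = 106 enrolled.

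**The plan's own figure first.** 40 / (1 − 0.25) = 53.3, stated as 53. This agrees to rounding. (The 40 itself cannot be rebuilt, because no effect size or standard deviation is given. Nothing below depends on it except as a sample size.)

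**Assumptions, since the documents give no correlations.** One demographic factor has correlation r with the imaging value and r with the cognitive score. Given that factor, imaging and score are independent, so the marker has no link of its own to cognition. The test is two-sided at 0.05.

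**Formula.** The induced marginal correlation is r × r = r². By Fisher's z, the test statistic is approximately normal with mean m = atanh(r²) × √(n − 3) and unit variance. The rejection probability is Φ(m − 1.96) + Φ(−m − 1.96).

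For n = 80, √77 = 8.775. With r = 0.4: r² = 0.16, atanh(0.16) = 0.1614, m = 0.1614 × 8.775 = 1.416. The rejection probability is Φ(−0.544) + Φ(−3.376) = 0.294.

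| r | r² | m, n = 80 | Fisher z, n = 80 | Simulated, n = 80 | Fisher z, n = 106 | Simulated, n = 106 |
|---|---|---|---|---|---|---|
| 0.2 | 0.04 | 0.351 | 6.4% | 6.0% | 6.9% | 6.8% |
| 0.3 | 0.09 | 0.792 | 12.4% | 12.5% | 15.0% | 14.7% |
| 0.4 | 0.16 | 1.416 | 29.4% | 30.5% | 37.4% | 37.1% |
| 0.5 | 0.25 | 2.241 | 61.1% | 61.8% | 73.6% | 73.4% |

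The simulation used 10,000 trials per row. With age, sex and education in the model it rejected in 4.8% to 5.4% of trials in every scenario. If age and education each correlate 0.3 with both variables, the induced correlation is 0.09 + 0.09 = 0.18, and the simulated unadjusted rate is 36.8% (n = 80) or 45.5% (n = 106).

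**Sensitivity to the threshold.** The level for this regression is not explicit. The section states 0.05 with the neuropsychological comparisons and 0.005 with the imaging maps. At 0.005 and n = 80 the simulated rates for r = 0.2, 0.3, 0.4 and 0.5 are 0.7%, 2.3%, 8.4% and 28.4%, against a nominal 0.5%.

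**Sensitivity to ventricular volume.** Suppose it entered this model and had correlation ρ with the demographic factor (again an assumption). The remaining correlation is r²(1 − ρ²) / (1 − r²ρ²). For r = 0.4:

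- ρ = 0.5 gives 0.16 × 0.75 / 0.96 = 0.125.
- ρ = 0.7 gives 0.16 × 0.51 / 0.9216 = 0.0885.

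With one covariate, m = atanh(·) × √76, and the rejection rate at n = 80 falls from about 30% to about 19% and 12%.

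**The case against.** **Silence is not a statement.** The plan does not call the regression simple or unadjusted, and a journal article condenses a fuller protocol. A reader might infer that the sponsor has decided to leave the demographics out. The text does not support that. What does stand is the contrast within one section: covariates are named for the ANCOVA, for the post-hoc tests and for ReHo/ALFF, but not for this model. The Discussion also declares and explains one deliberate non-adjustment, for medication, and says nothing similar about demographics. This makes it a point about consistency rather than a request for more detail.

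**The selection link is inferred.** A reader might conclude that this regression chooses the ROC parameter. The order of the two sentences suggests it, but what counts as most sensitive is undefined, the group comparisons come just before, and the Discussion also points to choice by area under the curve. The objection stands: a confounded slope may not be what decides the marker.

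**Ventricular volume may take up part of an age effect.** The Discussion describes it broadly, as standing for structural change in the whole brain. The plan does not say that it enters this regression, and it would not cover schooling or sex.

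**The bias may be small.** The 40–60 age range and the education minimum limit the gradients. At a correlation of 0.2 the excess over 5% is one to two percentage points. This stands in full.

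**Conclusion.** The point holds in a limited form. The protocol article names gender, age and education as covariates for the cognitive scores, but not in the model that relates those scores to imaging. Run as written, that model can credit an age or schooling gradient to an MRI parameter. The chance of this runs from close to nominal at assumed correlations of 0.2 to about 61% (n = 80) or 74% (n = 106) at 0.5. These figures rest on equal correlations with marker and score, no true link between them, and an alpha of 0.05. None of the three is given in the documents.

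It is not established that the final marker will be one of ageing or schooling, that the model is meant to be unadjusted, or that the regression alone determines what enters the ROC. The change is worth making because it costs almost nothing and brings the regression into line with the ANCOVA.

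**What to change.** In the sentence on the linear regression, state that gender, age and years of education are included as covariates, as in the ANCOVA, and that any selection made from this regression rests on the adjusted imaging coefficient. Because the Discussion also points to choice by area under the curve, the sponsor may in addition report the AUC of the demographics alone next to that of the demographics plus the MRI parameter. This second step is optional.

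The cost is one sentence and 3 degrees of freedom: residual degrees of freedom go from 78 to 75 at n = 80, or from 104 to 101 at n = 106. No new data are needed, since the ANCOVA already requires the three variables. The reported associations may turn out smaller than the unadjusted ones.

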## Background

The prevalence of type 2 diabetes mellitus (T2DM) is rapidly increasing, making T2DM currently a major health challenge all over the world. Epidemiological studies showed that the T2DM was associated with a 1.5–2.5-fold increased risk of dementia [1]. Mild cognitive impairment (MCI) frequently occurs in T2DM population at a rate of 17.2 % [2] and consequently leads to dementia [3–5]. Moreover, MCI occurs at as early as the prodromal diabetic stage, making the early diagnosis of MCI an important strategy for decision making in T2DM treatment, especially for the prevention of T2DM related dementia.

MCI is currently diagnosed based on clinical criteria [6], mainly the cognition evaluation, however, with bias derived from the subjective nature of these cognition assessing tools. Other relatively objective neuroimaging biomarkers are proposed to detect T2DM related brain alterations that are supposed to be the underlying mechanisms for MCI or dementia. T2DM related MCI may be partly due to neuroanatomical alterations revealed by structural magnetic resonance imaging (sMRI), including atrophy in prefrontal cortex and the anterior cingulate [7–9]. Findings from diffusion tensor imaging (DTI) studies further indicated decreased fractional anisotropy values in frontal white matter [10], cingulum bundle, uncinate fasciculus [11], and anterior limb of internal capsule [12] in T2DM patients. Resting-state functional magnetic resonance imaging (rs-fMRI) studies demonstrated disrupted functional connectivity within the default mode network and decreased spontaneous brain activity in the occipital lobe and post central gyrus in T2DM patients [11, 13, 14]. A most recent study suggested the impaired macromolecular protein pools in fronto-striato-thalamic circuits in T2DM [15]. However, these findings can only be detected at the late stage of T2DM, thus cannot be used to screen MCI at the prodromal diabetic stage.

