MoCA is verified to be a valid scale for MCI in diabetes in China [32]. Different dimensions scores of MoCA will be calculated and analyzed together with imaging presentations. Therefore, we may detect the functional node for different cognitive dimensions. The association may help to speculate prognosis. The neuropsychological test battery comprises another four scales. They test the condition of cognition, affection and life style. Different cognitive-related circuits overlap and interact significantly. Therefore, affective and life style state evaluation is necessary for matching the changes of cerebral functional imaging presentations.

Treatment strategies vary significantly. According to our preliminary experiment, patients took metformin either alone or in combination with other drugs. Some of the diabetes went on insulin treatment. Part of the prediabetes group took statin-related drugs. Antihypertensive drugs were also taken by some individuals to control their blood pressure. Medications related to cardiovascular disease affect cerebral perfusion significantly [27], and they may play a role in neuronal plasticity as well [26]. In the current study, we have not taken medication therapies as covariant for some practice and ethics issues. The reliability of results may be affected by the disaccord of medication therapies.

Future studies should focus on comparing the imaging characteristics between MCI converted group and no converted group. Gene type may serve as a control condition. Other techniques such as using MRS for the metabolic data could be useful and should be evaluated as well. The consistency of therapeutic regimen should also be guaranteed.

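### Imaging parameters are selected, given cut-offs and scored for accuracy in the only cohort described, so the reported accuracy for MCI will be biased upward

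*Protocol article*

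**What the plan says.** In the section Sample size calculation and statistics, imaging values are related to cognitive test scores by linear regression across the T2DM and prediabetes groups. The next step is: "When the most sensitive parameters are found, a receiver operating characteristic (ROC) curve will be generated to achieve the sensitivity and specificity". The stated purpose of that curve is early detection of cognitive decline.

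The Discussion describes a further choice, "It may be revealed which one or combined protocols may express the highest area under curve by drawing ROC curve", and then the use of the result: "Corresponding sensitivity and specificity are calculated, and then we will get the cutoff values to diagnose MCI". The comparison that bears most directly on early detection is left for later work: "Future studies should focus on comparing the imaging characteristics between MCI converted group and no converted group".

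The candidate list is long and open. It covers regional CBF by gyrus, ALFF and ReHo (MRI image analysis), and volumetric, relaxation, diffusion, kurtosis, connectivity and graph measures (Primary outcome measure). The Abstract says that MCI is determined by MoCA. The only MCI rate given is in the Background: it "frequently occurs in T2DM population at a rate of 17.2" per cent.

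**The concern.** Three choices are made on the data: which parameter, which combination and which cut-off. Each favours whatever looks best in this sample. If accuracy is then read off the same subjects, part of it is the reward for having searched. With few MCI cases that part can be large relative to any real signal.

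The article presents the product as cut-offs to diagnose MCI, without qualification. A reader could carry a threshold and a sensitivity into practice that would not hold in new patients.

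The ROC outcome is also worded in two ways: decline in cognition in the statistics section, and diagnosis of MCI in the Discussion. These are different reference outcomes, and only an analysis against a later outcome would earn the word early.

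**Working it through.** **The plan's own sample size.** It is set for comparing group means: "A sample size of 40 patients per group will be suitable with a power of 0.8, an alpha significance level of 0.05 (two-side"), and then "Given a drop-out ratio of included subjects, at 25 %, into account, the total sample size is 53 in each group". 40/(1 − 0.25) = 53.3, so 53 reproduces to within rounding. The 40 cannot be rederived because no effect size or SD is given. Neither figure concerns MCI cases or diagnostic accuracy.

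**Expected MCI cases** (n × 0.172; the rate is for T2DM only).
- T2DM group: 53 × 0.172 = 9.1. After 25% drop-out: 40 × 0.172 = 6.9.
- T2DM plus prodromal, assuming the same rate in both: 106 × 0.172 = 18.2. After drop-out: 80 × 0.172 = 13.8.
- All three groups at that rate: 159 × 0.172 = 27.3.

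The illustrations use 9 cases against 44 non-cases (53 subjects) and 18 against 88 (106 subjects).

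**Precision of sensitivity** (exact Clopper-Pearson 95% CI).
- 7/9 = 0.78: 0.40 to 0.97.
- 14/18 = 0.78: 0.52 to 0.94.

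**Optimism from noise, by simulation.** Every candidate is independent and uninformative (true AUC 0.50). Two selection rules are tried because the article describes both:
- *Regression*: take the candidate with the strongest linear relation to a continuous score whose lowest 17% are labelled MCI, then draw the ROC in the same subjects.
- *Highest AUC*: take the candidate with the largest AUC in either direction.

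The number of candidates K is an assumption. K = 15 is the number of non-empty subsets of four modalities (2⁴ − 1). K = 50 stands for regions and measures within modalities.

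| Mean apparent AUC | K = 15 | K = 50 |
|---|---|---|
| 18 vs 88, regression | 0.60 | 0.62–0.63 |
| 18 vs 88, highest AUC | 0.65–0.66 | 0.69 |
| 9 vs 44, regression | 0.64 | 0.67 |
| 9 vs 44, highest AUC | 0.72 | 0.76 |

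Ranges show the spread between simulation runs. For reference, one noise marker with no selection but a free choice of direction already gives about 0.56 (18 vs 88) or 0.58 (9 vs 44).

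**Optimism with real signal** (20 markers, each of true AUC 0.70, highest-AUC rule).
- 18 vs 88: apparent AUC 0.82, a gain of 0.82 − 0.70 = 0.12.
- 9 vs 44: apparent AUC 0.87, a gain of 0.17.
- With markers correlated at 0.5: 0.79 and 0.82, gains of 0.09 and 0.12.

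**The case against.** Several points on the other side are sound.

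- **The size is not fixed by the text.** The statistics section selects by regression, which inflates the AUC less than picking the highest AUC. The latter appears only in the Discussion. K is not stated. A reader might infer that noise would be reported with an impressive AUC. Under the regression rule with 18 cases it would be about 0.60 to 0.63, which is biased but not impressive.
- **Much of the noise sensitivity is not selection among markers.** At 18 vs 88 a single noise marker with the best-looking (Youden) cut-off shows about 0.64 sensitivity and 0.57 specificity. The choice of cut-off and direction alone does this.
- **9 to 18 cases is derived, not stated.** The upper figure borrows a T2DM rate for the prodromal group. Controls may enter the ROC, and cases arising over six visits would add to the count. Drop-out would lower it.
- **Same-visit analysis is not in the text.** A reader might infer that the ROC sets MRI against MoCA at one visit and therefore cannot support early detection. The article ties the ROC to no visit, and MRI and MoCA are both repeated over 2.5 years, so the cohort could support such an analysis.
- **A condensed article may omit validation detail.** That is fair for the resampling method, the MoCA threshold and the visit. It does not cover the unqualified promise of diagnostic cut-offs after a stated select-then-ROC sequence.
- **Accuracy is not the primary outcome.** That is group differences in MRI measures, and the diagnosing system is something the authors hope to establish. This lowers the severity and leaves the bias in place.

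**Conclusion.** The point holds in this form: followed as written, the plan gives upward-biased AUC, sensitivity and specificity, and turns them into cut-offs described as diagnostic. The direction does not depend on the assumptions. The size does. For uninformative measures, the mean apparent AUC is about 0.60 to 0.69 with 18 cases and 0.64 to 0.76 with 9, given 15 to 50 independent candidates and the two selection rules; correlation among measures would lower these figures. Use of the same subjects for selection and evaluation is inferred from there being only one cohort and no described split or resampling.

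The documents do not support the stronger claims that the study cannot address early detection, or that the inflation has a known large size. The two descriptions of the ROC outcome do need to be reconciled. This should be fixed before analysis. It does not undermine the primary group comparison.

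**What to change.** 1. Repeat the whole sequence (screening, combination, cut-off) inside each bootstrap sample, or in nested cross-validation. The bootstrap is preferable with so few cases. Report optimism-corrected AUC, sensitivity and specificity with 95% CIs, and state the number of candidate parameters.
2. Replace the promise of diagnostic cut-offs with exploratory cut-offs that need external validation. State the expected number of MCI cases, with the assumed rate for each group.
3. Name one ROC outcome. Keep the word early for an analysis of baseline MRI against later MoCA-defined MCI in subjects free of MCI at baseline. Report it as supportive: the article gives no incidence, and new cases may be very few.

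The cost is analysis and rewording only, with no new data. Reported accuracy will look lower and less precise, and resampling with about 9 cases will itself be unstable.

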## Abstract

**Background:**

Type 2 diabetes mellitus (T2DM) is a risk factor for dementia. Mild cognitive impairment (MCI), an intermediary state between normal cognition and dementia, often occurs during the prodromal diabetic stage, making early diagnosis and intervention of MCI very important. Latest neuroimaging techniques revealed some underlying microstructure alterations for diabetic MCI, from certain aspects. But there still lacks an integrated multimodal MRI system to detect early neuroimaging changes in diabetic MCI patients. Thus, we intended to conduct a diagnostic trial using multimodal MRI techniques to detect early diabetic MCI that is determined by the Montreal Cognitive Assessment (MoCA).

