Previous studies suggested that the brain microvascular alterations might explain MCI. A positron emission tomography-computed tomography study revealed that the focal brain blood decrease occured at as early as several years before Alzheimer`s disease diagnosis and was accompanied with the MCI progression [16]. On the contrary, a trend to a slight cerebral blood flow (CBF) increase in bilateral hippocampi and the posterior cingulate gyrus among patients with MCI was noticed using dynamic susceptibility contrast MRI [17]. The major shortcoming of these methods to measure CBF is the use of radio-labeled contrast agents, thus, not suitable for screening brain microvascular alterations in the prodromal diabetic population. Three-dimensional pseudo-continuous arterial spin labeling (3D-pCASL), a non-invasive and non-contrast perfusion imaging method [18], is commonly used to measure CBF alterations and demonstrates equivalent diagnostic performance to Single-photon emission computed tomography (SPECT) for Alzheimer`s disease [19].

Thus, we designed the current prospective diagnostic trial for 2 purposes. First, to investigate the structure, functional alterations and gray/white matter integrity with sMRI, fMRI and diffusional kurtosis imaging (DKI, also measures non-Gaussian diffusion and may provide additional and complementary information to DTI [20]) in prodromal diabetic population, respectively. Second, to investigate the early brain microvascular alterations by using 3D-pCASL.We hope to establish an integrated diagnosing system for early MCI in prodromal diabetic population by using multimodal MRI techniques.

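### The statistics section stops at an ROC curve for a single parameter and never forms the combined multimodal score that the aim and the Discussion rely on

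*Protocol article*

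**What the plan says.** The Abstract gives the gap to be filled: "there still lacks an integrated multimodal MRI system to detect early neuroimaging changes in diabetic MCI patients". The Background closes with the authors' "hope to establish an integrated diagnosing system for early MCI in prodromal diabetic population by using multimodal MRI techniques".

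The article sets out its inferential analyses under *Sample size calculation and statistics*. After the group comparisons, that section plans a linear regression across the T2DM and prediabetes groups "to assess relationships between imaging values and cognitive testing scores". It continues: "When the most sensitive parameters are found, a receiver operating characteristic (ROC) curve will be generated", and the purpose of that curve is "to achieve the sensitivity and specificity of the certain parameter for early detection of the cognitive decline".

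The Discussion describes a wider analysis. It says "multi-modal sequences will be conducted and analyzed at the same time" and then "It may be revealed which one or combined protocols may express the highest area under curve by drawing ROC curve". Sensitivity, specificity and MCI cutoffs are to follow from that comparison.

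The image-analysis subsections process sMRI, 3D-pCASL, DKI and rs-fMRI separately. The one stated link between modalities is ventricular volume as a covariate for ReHo and ALFF. That adjusts for atrophy and does not combine modalities into a classifier.

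**The concern.** An ROC curve needs one number per person. A single parameter supplies that number directly, but a combination of modalities supplies it only after a rule has merged them. The Discussion's comparison therefore cannot be run from the steps in the statistics section.

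At stake is the diagnostic claim. If the statistics section governs, the trial reports accuracies of separate parameters and cannot say whether the modalities together do better than one. If the Discussion governs, the winner is chosen by its AUC in the people who also supply the reported AUC and cutoff, from a long list of candidate measures (see *Primary outcome measure*). That AUC will be too high, and the fewer the MCI cases, the larger the excess.

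**Working it through.** **1. The sections side by side**

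| Place | What goes to the ROC | Rule that merges modalities |
|---|---|---|
| Background (aim) | an integrated system | not expected there |
| Sample size calculation and statistics | one parameter, after selection of the best ones | none |
| Discussion | one or several sequences, ranked by AUC, then cutoffs | none |

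**2. The plan's own figure.** 40 evaluable per group with 25% dropout: 40 / (1 − 0.25) = 53.3, against 53 stated. This agrees. The 40 comes from a formula for comparing group means, so it does not speak to ROC precision.

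**3. MCI cases available.** The regression spans both case groups: 2 × 53 = 106 recruited, or 2 × 40 = 80 completers. The Background gives 17.2% MCI in T2DM. Applying that rate to the prodromal group as well is an assumption.

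- Recruited: 106 × 0.172 = 18.2 cases; 18.2 / 4 modalities = 4.6 per predictor.
- Completers: 80 × 0.172 = 13.8 cases; 13.8 / 4 = 3.4 per predictor.
- Range for assumed rates of 10% to 30%: 8 to 24 cases among 80, and about 11 to 32 among 106.

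**4. Precision of one AUC (Hanley–McNeil).** With a = A/(2 − A) and b = 2A²/(1 + A),

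SE² = [A(1 − A) + (n₁ − 1)(a − A²) + (n₀ − 1)(b − A²)] / (n₁n₀).

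For an assumed A = 0.80, a = 0.667 and b = 0.711.

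- n₁ = 14, n₀ = 66: SE = 0.0745, and 1.96 × SE = 0.146.
- n₁ = 18, n₀ = 88: SE = 0.0655, and 1.96 × SE = 0.128.

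A single AUC is thus known to about ±0.13 to ±0.15, before any selection.

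**5. Optimism from selecting and fitting in the same people.** Simulation with assumed inputs: 80 people; a continuous cognitive score, with MCI as the worst 17.2%; four modalities, each with a true AUC of 0.65; correlation between modalities 0.2 or 0.5. The combined score is a ridge model (penalty 10) of the continuous score on the four modalities plus four uninformative clinical covariates.

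| Correlation | Best single, apparent (true 0.65) | Combined, apparent | Combined, new subjects |
|---|---|---|---|
| 0.2 | about 0.73 | 0.77–0.78 | 0.70–0.71 |
| 0.5 | about 0.71 | about 0.74 | about 0.66 |

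Choosing the best single modality by itself inflates the AUC by about 0.06 to 0.08. Fitting a combined score without validation inflates it by a similar amount. The SD of the apparent gain of combined over best single is about 0.04.

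**6. Ceiling on the gain from combining.** A single AUC of 0.65 is a separation d = √2 × z(0.65) = 0.545. With ideal weights the combined separation is d√(4/(1 + 3ρ)): 0.862 at ρ = 0.2 and 0.689 at ρ = 0.5. AUC = Φ(d/√2) gives 0.729 and 0.687, a gain of 0.079 and 0.037. This assumes known weights and no estimation loss.

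**The case against.** The strongest reply is that the article does intend a combined analysis. The Discussion says so, the statistics section speaks of parameters in the plural before narrowing to one, and nothing limits the regression to one predictor at a time. The merging formula is also detail that a condensed article may leave to a full protocol or SAP. All of this stands. A reader might infer that the integrated system is never estimated; the documents do not support that, because the Discussion plans an ROC comparison that includes combinations. The missing formula alone would be no finding. What remains is that the two sections describe different diagnostic analyses, and the section that should govern is the narrower one.

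Three other inferences go too far.

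- *That the trial will lose 0.04 to 0.08 of AUC.* This is the ceiling in step 6, under assumed inputs and ideal weights. At correlation 0.5, the fitted model in new subjects barely exceeded a single modality.
- *That a combined model has only about two cases per predictor.* This counts one group of 53 (53 × 0.172 = 9.1; 9.1 / 4 = 2.3), whereas the planned regression uses both case groups.
- *That MRI must be shown to add to age, education and HbA1c.* The article nowhere promises this.

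It is also fair that the integrated system is worded as a hope, and that the primary outcome is group differences in MRI measures. Those comparisons are unaffected.

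**Conclusion.** The point holds as a mismatch. The Background and Discussion call for a combined multimodal classifier with MCI cutoffs, while the statistics section specifies an ROC for one selected parameter and no step that forms a combined score.

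The consequence is either an unanswered question about combination or an optimistic answer to it. Under the assumptions in step 5, the optimism is about 0.06 to 0.08 of AUC, with about 14 to 18 MCI cases behind it. That count depends on applying the 17.2% T2DM rate to both case groups; a lower rate in the prodromal group would leave fewer cases. The text mismatch depends on none of these assumptions. The sponsor should correct it, since the diagnostic aim depends on it.

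**What to change.** In *Sample size calculation and statistics*, and consistently in the Discussion:

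1. Name one summary measure per modality (sMRI, 3D-pCASL, DKI, rs-fMRI) before the data are examined.
2. Pre-specify one penalised model across the four. Continuous MoCA is a reasonable outcome given the few MCI cases.
3. Take the cross-validated or bootstrap optimism-corrected score to the ROC for MoCA-defined MCI, and derive the cutoff within the same validation.
4. Compare its AUC with that of the best single modality. Repeat the choice of best modality inside each resample, so that the correction covers the selection too.
5. Label the single-parameter ROCs as descriptive. A comparison with clinical variables alone is optional.

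The validation in step 3 is essential: a combined model scored in the people it was fitted to would show the inflated values in the simulation.

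The cost is one more analysis on data already planned for collection. The corrected AUC and gain will be smaller and less precise than the apparent ones, and the trial may be unable to show that combining helps.
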